### Outcome Measures

The primary measure is the number of participants who have obtained, or have updated, their written asthma action plan with a GP within the 12 months of the study. The secondary outcomes concern actual use rate of the written asthma action plan, number of unplanned visit to healthcare for asthma, usage of *Healthy.me*, asthma symptoms, and competing demands on health and asthma. Please see Table 1 below.

**Table 1 table1:** Summary of outcome measures.

Outcome measures		Measurement time points & methods		Time	
			Baseline	Monthly	Completion

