**Results:**

The primary outcome measure is possession of or revision of an asthma action plan during the study. Secondary outcome measures include: (1) adherence to the asthma action plan, (2) rate of planned and unplanned visits to healthcare providers for asthma issues, (3) usage patterns of Healthy.me and attrition rates, (4) asthma control and asthma exacerbation scores, and (5) impact of asthma on life and competing demands, and days lost from work.

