### Study Aims and Hypotheses

Specific hypotheses to be tested in this study are that:

Consumers using a Web-based PCHMS with interactive and social features are more likely to follow evidence-based guideline recommendations for asthma management, as measured by the rates of obtaining or updating a written asthma action plan with their GP and the usage rates with the asthma action plan, measured by questionnaires;Use of a PCHMS will contribute to improved asthma control and reduced rates of asthma exacerbation compared to those using only static websites (usual care arm).

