### Sample Size

A conservative estimate of at least 300 participants with 150 in each arm is needed to detect a 15% point difference in possession rate of a written asthma action plan between the control group (14.4%) and the intervention group (29.4%). This estimate is calculated at 5% level of significance, 80% power (2-sided test), with an anticipated participant dropout rate approximately 25%.

The effect size estimate is based on previous studies using *Healthy.me* assessing the efficacy of Internet-based interventions on the uptake of preventative health actions [23], and on studies with interventions promoting the use of personal asthma action plans [13]. The base rate is the percentage of adults (ie, 15 years and over) with current asthma in Australia and possessing a written asthma action plan, reported in the Australia Centre for Asthma Monitoring analysis of the Australian Bureau of Statistics National Health Survey 2007-2008, and cited in the Australia Centre for Asthma Monitoring 2011 report [2].

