**Primary outcome**					
	Number of participants with a written asthma action plan	Pre and post-study surveys	X		X

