**Secondary outcomes**					
	Number of participants reported using their written asthma action plan, obtained, or updated during the study	Post-study survey	X		X
	Rate of planned (non-urgent) visits to a healthcare professional (eg, GP) for routine asthma management	Post-study survey			X
	Rate of unplanned visits to a GP, emergency department, caused by worsening asthma	Post-study survey			X
	Website usage patterns (number and timing of hits, duration of access, uptake of specific functions) of *Healthy.me*	*Healthy.me* system logs			X
	Technology acceptance of *Healthy.me*	Measured via the “Scales for Perceived Usefulness and Perceived Ease of Use” [30]			X
	Asthma control	Measured via “Asthma Control Questionnaire” [31]		X	
	Asthma exacerbations	Measured via the “Asthma Exacerbation Questionnaire” [32]		X	
	Number of days lost from work or school	Measured via an additional question after the “Asthma Control Questionnaire” [31]		X	
	Competing demands on health and asthma	Lists of life priorities and top health issues, monthly made by participants.		X	
					
					
					

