#### Primary Analysis

Differences in proportions of participants visiting their GP to obtain/update their written asthma action plan during the study will be compared between control and PCHMS groups. All intervention recipients who had the opportunity to use the PCHMS but did not do so will be included in the primary analysis (intention-to-treat principle with Last Observation Carried Forward (LOCF) imputation procedure for missing values [35,36]). Differences in participant proportions between control and PCHMS groups will be analyzed using χ^2^test or Student’s *t*-test. Proportions will be reported with 95% confidence intervals. Adjustments for baseline characteristics and possible confounders, such as age and other demographics [2,3], smoking status [3], and asthma severity [2], will be made through the use of sequential logistic regression [37]. All baseline characteristics, and factors that may affect the written asthma action plan possession rate collected at post study (eg, past possession of an asthma action plan) will be entered at step 1 of the regression; and group allocation (PCHMS vs. control) will be entered at step 2.

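### The single primary outcome is defined inconsistently, as obtaining or updating a plan and as having one, and the planning rate belongs only to having one

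*Protocol article*

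**What the plan says.** All references are to the protocol article. The primary outcome appears in six places.

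**As an event during the study**
- Study Aims and Hypotheses: "rates of obtaining or updating a written asthma action plan with their GP".
- The section on Outcome Measures has: "The primary measure is the number of participants who have obtained, or have updated, their written asthma action plan with a GP". The count covers the 12-month study, and the paragraph then sends the reader to Table 1.
- Primary Analysis: the compared proportions are of "participants visiting their GP to obtain/update their written asthma action plan during the study".

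**As a state**
- Table 1, primary outcome row: "Number of participants with a written asthma action plan", from the pre- and post-study surveys and marked at baseline and completion.
- Sample Size: a 15-point "difference in possession rate of a written asthma action plan between the control group (14.4%) and the intervention group (29.4"%).

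**As a mixture**
- Abstract, Results: "possession of or revision of an asthma action plan during the study".

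In Table 1 the obtained-or-updated wording appears only in a secondary row, on plan use: "Number of participants reported using their written asthma action plan, obtained, or updated during the study". Primary Analysis, having named the event, later refers to factors that affect the possession rate. It also specifies last observation carried forward (LOCF) for missing values.

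Sample Size gives the source of the 14.4%: the share of people aged 15 and over with current asthma who possessed a written plan in a 2007-2008 national survey.

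**The concern.** Holding a plan is not an exclusion criterion, and both Primary Analysis and Limitations anticipate participants with a previous plan. For a participant who enters with a plan and neither replaces nor revises it, the event definition records a failure and the state definition a success. The two variables therefore differ for a group that the protocol expects to enrol.

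Three things are at stake. First, no sentence says which definition governs where they conflict, so either result could later be presented as prespecified. Second, the sample size was calculated for one quantity and the test is specified on another. Third, LOCF behaves differently under each definition: baseline possession can be carried forward to month 12, but an event that can only happen after randomisation has no baseline value to carry.

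**Working it through.** **1. Reproduce the plan's figure.** Inputs from Sample Size: p1 = 0.144, p2 = 0.294, two-sided 5%, 80% power, about 25% dropout, 300 in total.

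Pooled-variance formula: n = [1.96·√(2p̄(1−p̄)) + 0.842·√(p1(1−p1) + p2(1−p2))]² / (p2−p1)², with p̄ = 0.219.

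n = [1.96 × 0.585 + 0.842 × 0.575]² / 0.0225 ≈ 118.1, so 119 per arm. Then 119 × 1.25 ≈ 149 per arm, 298 in total, which matches 300. The stated size thus follows from the possession rates. (Dividing by 0.75 instead gives 159 per arm, 318 in total; that is a side point.)

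After 25% loss, 150 × 0.75 = 112.5, so 112 per arm are used below. Power is Φ{(Δ − 1.96·SE0)/SE1}, where SE0 = √(2p̄(1−p̄)/n) and SE1 = √([p1(1−p1) + p2(1−p2)]/n). For 14.4% vs 29.4% this gives 78%.

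**2. Compare the definitions on the same participants.** The protocol gives neither the baseline possession rate in the trial nor a 12-month obtain/update rate, so these inputs are assumptions. A share b hold a plan at entry, 14.4% vs 29.4% of non-holders obtain one, holders do not update, and no plans are lost.

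- Event rate = (1−b)·p
- Possession rate = b + (1−b)·p
- Difference under either = (1−b) × 0.15

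| b | Definition | Control | Intervention | Difference | Power, 112 per arm |
|---|---|---|---|---|---|
| 14.4% | Event | 12.3% | 25.2% | 12.8 points | 69% |
| 14.4% | Possession | 26.7% | 39.6% | 12.8 points | 53% |
| 30% | Event | 10.1% | 20.6% | 10.5 points | 59% |
| 30% | Possession | 40.1% | 50.6% | 10.5 points | 35% |

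The absolute difference is the same under both definitions. Power is lower for possession because its base rate, and hence its variance, is higher. The fall from 15 points comes from the factor (1−b), which applies to both.

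**3. Let updating differ by arm.** Assume b = 14.4%, 20% vs 50% of holders update, and 10% vs 20% of non-holders obtain a plan.

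- Event: 0.144 × 0.20 + 0.856 × 0.10 = 11.4%, against 0.144 × 0.50 + 0.856 × 0.20 = 24.3%. Difference 12.9 points, power 71%.
- Possession: 0.144 + 0.856 × 0.10 = 23.0%, against 0.144 + 0.856 × 0.20 = 31.5%. Difference 8.6 points, power 30%.

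The estimates themselves now separate, because possession cannot register updating by holders.

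**4. Power for the event when its control rate is unknown.** Keep a 15-point difference and 112 per arm.

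| Control rate | 5% | 10% | 14.4% | 20% | 30% | 40% |
|---|---|---|---|---|---|---|
| Power | 93% | 84% | 78% | 71% | 64% | 61% |

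**The case against.** The best defence is that there is only one primary outcome and its meaning is recoverable. The hypothesis, the sentence that defines the measure and the paragraph that specifies the test all describe the event. The Table 1 row can be read as shorthand in a summary table. This largely stands: a reader might infer that the trial has two primary endpoints, but the document declares one and labels it loosely elsewhere. It does not remove the conflict, because the defining paragraph points to that table, and the possession wording in Sample Size is the stated basis of the calculation.

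A reader might also infer that the endpoint is open to choice after the results are seen. Primary Analysis names the variable to be compared, and the allocation section keeps investigators blinded until the quantitative analyses are complete. These reduce the risk without closing it.

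It is also tempting to say that counting baseline holders as successes shrinks the treatment difference. Adding the same share to both arms does not change an absolute difference, as step 2 shows; only a difference between arms in updating separates the estimates. Nor is the power gap a fixed quantity. If 30% of holders update in each arm, event power falls to 63% (b = 14.4%) and 45% (b = 30%), against 53% and 35% for possession, so the gap narrows to about 10 points.

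Limitations already concedes that the volunteers may not represent people with asthma generally. That bears on the choice of base rate, not on the inconsistent definition.

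**Conclusion.** The inconsistency is in the text and should be corrected. Three places define an event, two a state and one a mixture, and the sample size rests on the state while the primary test is of the event. The definitions can give different results but need not; that depends on how many participants hold a plan at entry and on how updating differs between arms.

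Under the stated assumptions with no updating, the effect is the same on either definition, and power is about 69% (event) against 53% (possession), or 59% against 35%, at 14.4% and 30% baseline possession. A reader might conclude that the trial is underpowered for its primary test. The documents do not support that: the control rate for obtaining or updating is unknown, and for a 15-point difference power could be above or below the stated 80%. What can be said is that the stated power describes a different quantity from the one to be tested.

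**What to change.** - Use one definition in the Abstract, Sample Size and the Table 1 primary row, matching Outcome Measures and Primary Analysis: obtained a first written plan, or updated an existing one, with a GP between randomisation and month 12, yes or no.
- Report possession at the end of the study as a secondary outcome. Keep baseline possession as a covariate; Primary Analysis already names past possession among the factors for adjustment.
- In Sample Size, state that 14.4% is a population possession figure standing in for an unknown obtain/update rate. Simply relabelling it as an obtain/update rate would repeat the mismatch. Give power for a 15-point difference at 112 per arm over control rates of 5% to 40%, as in step 4.
- State how a missing event is handled, since LOCF has no baseline value to carry for it.

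The cost is rewording, and a single power figure that becomes a range and may look less favourable. Design and recruitment target are unchanged. The survey items are not shown, so confirm that the post-study survey asks both about possession and about obtaining or updating a plan with a GP during the study.

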**Primary outcome**					
	Number of participants with a written asthma action plan	Pre and post-study surveys	X		X
**Secondary outcomes**					
	Number of participants reported using their written asthma action plan, obtained, or updated during the study	Post-study survey	X		X
	Rate of planned (non-urgent) visits to a healthcare professional (eg, GP) for routine asthma management	Post-study survey			X
	Rate of unplanned visits to a GP, emergency department, caused by worsening asthma	Post-study survey			X
	Website usage patterns (number and timing of hits, duration of access, uptake of specific functions) of *Healthy.me*	*Healthy.me* system logs			X
	Technology acceptance of *Healthy.me*	Measured via the “Scales for Perceived Usefulness and Perceived Ease of Use” [30]			X
	Asthma control	Measured via “Asthma Control Questionnaire” [31]		X	
	Asthma exacerbations	Measured via the “Asthma Exacerbation Questionnaire” [32]		X	
	Number of days lost from work or school	Measured via an additional question after the “Asthma Control Questionnaire” [31]		X	
	Competing demands on health and asthma	Lists of life priorities and top health issues, monthly made by participants.		X	
					
					
					

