### Study Procedure

Table 3 below summarizes participant procedures in the study. The duration of the study is expected to be 12 months.

Email will be the primary channel to communicate with participants for study information and reminders about survey completion. From the time participants are recruited until study completion, all participants (control and intervention) will receive an email each month to complete a 5-minute survey about their health in the past month. At study completion, all participants will receive an email asking them to complete a post-study survey. In order to ensure the completeness of data collection, there will be 2 follow-up emails sent 5 days apart from each other to remind those who have not completed each survey.

**Table 2 table2:** Surveys used in the study.

Survey	Purpose
Screening survey	Eliciting participants’ eligibility criteria.
Pre-trial survey	To obtain participants’ demographics and experiences of asthma management at study enrolment.
Monthly follow-up questions	To obtain participants’ self-reported symptoms of asthma (ie, asthma control and exacerbation), impact on work and study due to asthma symptoms, and competing demands and health throughout the study.
Post-trial survey (12 months after the beginning of the study)	To obtain participants’ state of asthma control and asthma management. For those who receive the PCHMS version of *Healthy.me*, their perceived usefulness of *Healthy.me* will also be assessed.

**Table 3 table3:** Stages of study procedure.

Stage of study	Procedure

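### No baseline score is scheduled for asthma control, exacerbations or days lost, so the Hypothesis 2 comparison is unbiased but less precise than it could be

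*Protocol article*

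**What the plan says.** Hypothesis 2 (Study Aims and Hypotheses) reads: "Use of a PCHMS will contribute to improved asthma control and reduced rates of asthma exacerbation compared to those using only static websites".

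Table 1 (Outcome Measures) has three timing columns: Baseline, Monthly and Completion. Three outcomes are marked under Monthly alone: the "Asthma Control Questionnaire", the "Asthma Exacerbation Questionnaire" and "Number of days lost from work or school". The Baseline column is in use elsewhere in the table, for the primary outcome and for use of the action plan.

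Table 2 (Study Procedure) gives the pre-trial survey the purpose of obtaining "demographics and experiences of asthma management at study enrolment". It places control and exacerbation in the monthly follow-up questions, together with "impact on work and study due to asthma symptoms, and competing demands and health throughout the study". It also says that the post-trial survey obtains the "state of asthma control and asthma management".

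Secondary and Ancillary Analysis compares questionnaire scores and days of absence between the arms by a t-test or a non-parametric method. Adjustment for baseline characteristics appears only under Primary Analysis, for the action-plan outcome. The one disease measure named at entry is asthma severity in two levels, a stratification factor under Randomization.

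**The concern.** The outcomes of one of the trial's two hypotheses have no scheduled measurement before participants learn their arm. A pre-treatment value of the outcome is often a useful covariate, and it cannot be recovered once access has begun. Without it, three things are unavailable:

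- an adjusted and more precise between-arm estimate;
- a table showing how similar the arms were on asthma control at entry;
- change within a participant.

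The Limitations section itself says that baseline variables might influence outcomes and undertakes to identify them. The entry level of asthma control is a natural candidate, yet the schedule does not collect it.

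The monthly surveys are not a planned substitute. The date of the first one relative to randomisation is not given. Intervention participants have access from recruitment, and Allocation Concealment and Assessment says that the arm is revealed once the pre-study questionnaire is done. A monthly survey would therefore normally be answered with the arm known, even if its recall period reached back before allocation.

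**Working it through.** **Inputs**

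- From Sample Size: 150 per arm, 25% dropout, two-sided 5% significance, 80% power.
- Completers per arm: 150 × 0.75 = 112.5, taken as 112.
- Assumed: the correlation r between a baseline and a follow-up control score. The document gives none, so a range of 0.3 to 0.7 is shown.
- Assumed for illustration: a true difference of 0.30 SD.

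**The plan's own figure**

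The article gives no power figure for these secondary outcomes. Its sample size is for the primary outcome, 14.4% against 29.4%. With a pooled proportion of 0.219:

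- n = [1.96 × √(2 × 0.219 × 0.781) + 0.842 × √(0.144 × 0.856 + 0.294 × 0.706)]² / 0.15², which rounds up to 119 per arm.
- 119 × 1.25 = 149, in line with the stated 150.

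The present point takes only the number of completers from this.

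**Effect of a baseline covariate on a single follow-up score**

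- Variance factor: v = 1 − r² (v = 1 without a baseline).
- Detectable difference in SD units: (1.96 + 0.842) × √(2v/112).
- Power at 0.30 SD: Φ(0.30 / √(2v/112) − 1.96).

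Without a baseline, √(2/112) = 0.134, so the detectable difference is 2.802 × 0.1336 = 0.374 SD and the power is Φ(2.245 − 1.96) = 61%.

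| r (assumed) | v | Variance removed | Detectable difference (SD) | Power at 0.30 SD |
|---|---|---|---|---|
| no baseline | 1.00 | – | 0.374 | 61% |
| 0.3 | 0.91 | 9% | 0.357 | 65% |
| 0.5 | 0.75 | 25% | 0.324 | 74% |
| 0.6 | 0.64 | 36% | 0.300 | 80% |
| 0.7 | 0.51 | 49% | 0.267 | 88% |

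At r = 0.7 the remaining variance is 51% of the unadjusted variance, so 49% is removed.

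**Change score instead of covariate**

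A simple change from baseline has variance 2(1 − r) relative to the follow-up score alone: 1.4 at r = 0.3, 1.0 at 0.5 and 0.6 at 0.7. Below r = 0.5 it is noisier than having no baseline. The gain comes from using the baseline as a covariate, not from subtracting it.

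**Chance imbalance**

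The standard error of the baseline difference between arms is 0.134 SD. An imbalance of at least 0.2 SD in either direction has probability 2 × [1 − Φ(0.2/0.134)], about 13%. At r = 0.6 such an imbalance would move an unadjusted follow-up difference by 0.6 × 0.2 = 0.12 SD. As scheduled, it could not be seen.

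**The case against.** **Hypothesis 2 does not need a baseline.** A reader might infer from the word improved that the hypothesis cannot be tested without one. The documents do not support that. The hypothesis is a contrast with the static-website arm, the planned analysis is that contrast, and randomisation makes the follow-up comparison unbiased. Nor is chance imbalance a bias: its contribution is already in the standard error. This part of the objection stands in full and limits the point to precision, displayed balance and within-person change.

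**The absence is read from summary tables.** Table 1 is a summary, and it already seems to omit a completion time point that Table 2 implies. Table 2 gives one-line purposes, not item lists. The secondary analysis section mentions pre-study questionnaires as a data source, though for activities during the study. This tempers confidence. However, Table 1 uses its Baseline column for other outcomes, Table 2 agrees with it on where control and exacerbation belong, and no section names a baseline score.

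**Timing of the first monthly score.** One might infer that it always follows a full month of access. The article does not say so; part of its recall period might precede allocation.

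**Severity is balanced by stratification.** True, but two levels are a coarse proxy for a control score, and the secondary comparison does not use them. If all participants had moderate persistent asthma, as the Abstract describes, the factor would not vary, although the inclusion criteria set no such limit.

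**The gain may be small, or may come from elsewhere.** At r = 0.3 it is modest. Averaging monthly scores also helps. If all scores correlate equally at 0.6, the mean of 12 has variance (1 + 11 × 0.6)/12 = 0.633, so its detectable difference is 0.374 × √0.633, about 0.30 SD, with no baseline. Adding a baseline gives 0.633 − 0.36 = 0.273 and about 0.20 SD. It would be wrong to credit the whole fall from 0.374 to 0.20 to the baseline. It also needs 12 complete scores per person, whereas access lasts 9 to 12 months and the Limitations section expects attrition.

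**Conclusion.** The concern holds as a loss of efficiency and of information, not of validity. As documented, the three outcomes are scheduled only during follow-up and compared unadjusted. A separate analysis plan could add covariates, but not one that was never collected.

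The size depends on the unknown r: little is gained at 0.3 and a good deal at 0.7. The table above is for one continuous control score with 112 completers per arm. It does not carry over automatically to exacerbations or days lost, which may be counts or skewed and for which the plan allows non-parametric tests. The primary outcome is unaffected.

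Separately, Table 2 has asthma control recorded in the post-trial survey while Table 1 has no Completion mark for it. That inconsistency stands whatever is decided about the baseline.

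**What to change.** 1. Add the asthma control questionnaire to the pre-study survey, which is completed before the arm is revealed. Add the exacerbation and days-lost items too if survey length allows.
2. Mark Baseline in Table 1 for each item added, and state it in the Table 2 entry for the pre-trial survey.
3. Use each baseline value as a covariate in the between-arm analysis of its outcome. Recruitment is ongoing, so some participants will have no baseline score. A longitudinal model with a common baseline mean for both arms keeps them in the analysis.
4. Reconcile Tables 1 and 2 on whether asthma control is recorded at completion.

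The items already exist in the 5-minute monthly survey, so the cost is up to about 5 extra minutes on a 10-minute survey, a minor survey amendment and one covariate per model. The added length is a real drawback in a trial that expects attrition, so the control questionnaire should come first if not everything fits. No extra staff or procedures are needed.
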